## Abstract

Exercise may be an effective tool to improve symptoms and quality of life in those with endometriosis. However, the optimal dose to elicit such changes is unknown. This study will explore the critical threshold of exercise dose required to elicit symptomatic and biomarker changes in women with endometriosis, particularly for those who may be disadvantaged through spatial and aspatial factors.

Fifty women with clinically confirmed endometriosis will be randomly allocated into one of four groups: a passive control, active control (yoga), short duration walking and yoga, long duration walking and yoga.

Participants in the three active groups will complete 12 weeks of exercise.

Symptom severity (chronic) and biomarkers will be assessed pre-post intervention; adherence, and symptom impact (acute) will be assessed each week.

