Recent evidence suggests the management of endometriosis requires a multidisciplinary, life-course approach[8], extending beyond the reproductive system and incorporating physical and psychosocial elements, whilst acknowledging patient autonomy and self-management strategies[8].The importance of exercise and physical activity has gained increasing awareness as a viable non-pharmacological, non-surgical adjunct management strategy to support the quality of life of individuals with endometriosis[9]. Specifically, a recent meta-analysis reported physical activity and exercise to have beneficial effects on pain, quality of life, control and powerlessness and emotional well-being[10]. Exercise is widely recognized as an effective therapeutic intervention for pain management, fertility, cardiometabolic health, menstrual symptoms, indices of quality of life and improvement in inflammatory profiles[[11], [12], [13], [14], [15], [16]]. The potential of exercise to improve symptoms and quality of life in women living with endometriosis may be associated with immune and inflammatory modulation, regulation of autonomic function, musculoskeletal adaptations and reductions in central sensitisation[9]. However, globally, there are limited studies exploring specific exercise prescription (modality, volume, frequency and intensity) to improve symptoms, inflammation and quality of life. While emerging evidence suggests exercise has the capability to exert positive effects on symptoms, quality of life, biomarkers and even lesion size in endometriosis[[15], [16], [17], [18], [19], [20], [21], [22], [23]], to validate these findings, greater exploration into the exercise dose is required.

This study protocol has been designed to elucidate the critical threshold of exercise dose required to elicit changes in symptoms, quality of life, and biomarkers of endometriosis. By specifically detailing the exercise prescription, this protocol builds the evidence base for further scientific enquiry into exercise management in endometriosis. Further, this protocol provides clinical guidance to health and exercise professionals.

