## Data analysis

All data will be de-identified for analysis and reporting. The estimated sample size was determined using data from Gonçalves et al.[25] where the mean difference for pain between the control and intervention was 24.74, for an effect size of d = 1.33 and comparisons between four groups, a sample size of 32 was estimated (alpha at 0.05 and power 0.80). Factoring in attrition and funding availability, the target sample size was set to 50. However, a piecewise (segmented) mixed-effect regression will be used to determine the critical threshold for exercise dose (primary outcome). Exercise dose (all randomized participants) will be determined by duration and intensity (heart rate) variables, aggregated weekly. For a sample of 50 participants across 12 weeks, with a mixed-effects piecewise model, there will be a minimum of 600 observations, which provide sufficient power and stability for this type of analysis[26]. Threshold and detectable change in slope will be determined by Y^t^ = B^0^ + B^1^* time^t^ + b^2^ * intervention^t^ + b^3^ time after intervention^t^ + e^t^, and confirmed with Davies Test. Intercurrent events such as medication changes, clinical exacerbations and poor adherence will be time- and date-stamped for consideration as co-variates in the regression analysis.

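### The equation printed for the dose threshold has its slope change in time and no breakpoint on dose, so as printed it cannot return a threshold in dose units

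*Protocol article*

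**What the plan says.** The aim is stated twice. The Abstract has "This study will explore the critical threshold of exercise dose required to elicit symptomatic and biomarker changes in women with endometriosis", and the Background says the protocol is designed to "elucidate the critical threshold of exercise dose required to elicit changes in symptoms, quality of life, and biomarkers of endometriosis".

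The Data analysis section names the method: "a piecewise (segmented) mixed-effect regression will be used to determine the critical threshold for exercise dose (primary outcome"). It defines the exposure: "Exercise dose (all randomized participants) will be determined by duration and intensity (heart rate) variables, aggregated weekly". It then gives the working equation, which begins "Threshold and detectable change in slope will be determined by Y^t^ = B^0^ + B^1^* time^t^ + b^2^ * intervention^t" and is printed in full as "Y^t^ = B^0^ + B^1^* time^t^ + b^2^ * intervention^t^ + b^3^ time after intervention^t^ + e^t^, and confirmed with Davies Test".

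This is the only model equation in the article. The Specifications table also describes the regression as piecewise and mixed-effect. On information, the Data analysis section says that "there will be a minimum of 600 observations, which provide sufficient power and stability for this type of analysis".

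**The concern.** The section names dose as the quantity whose threshold is sought and defines how dose is measured, yet the equation said to determine the threshold does not contain it. The regressors are time, intervention and time after intervention, and the only subscript is t. This is the usual single-series interrupted-time-series form, which asks whether level and trend change when an intervention starts.

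What is at stake is the question the trial was set up to answer. If the equation is fitted as printed, the report can describe a shift or a change of trend over weeks, but not a threshold in minutes, training load or MET-minutes. If the mismatch is noticed only once data are in hand, the dose metric, the breakpoint search and the covariates would all be chosen after the event.

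**Working it through.** **1. The plan's own count.** 50 participants × 12 weeks = 600 rows. This reproduces the stated figure at full follow-up. The count does not bear on whether the model contains a dose breakpoint.

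**2. Term by term.**
- B0: level at the time origin.
- B1: change in Y per unit of time.
- b2: shift in level associated with intervention.
- b3: change of slope per unit of time after intervention.
- e: a single error term, with no participant index and no random effect.

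There is no parameter for a breakpoint on dose, and the change of slope is in time.

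**3. Can a reading of the intervention term supply the breakpoint?** The article does not define its coding, so each plausible reading was tried.
- *Arm indicator (0/1).* The break is the start of exercise. No dose breakpoint.
- *Step after week six*, when both walking groups increase (Exercise intervention section). The break is at a week known in advance. No dose breakpoint.
- *Weekly dose itself.* The dose effect is b2 × dose, a straight line with one slope everywhere. The slope change stays on time. No dose breakpoint.
- *A break week translated into a dose.* Prescribed weekly minutes just after week six are 0 (passive control), 3 × 10 = 30 (yoga), 30 + 90 = 120 (shorter) and 30 + 150 = 180 (longer). One week corresponds to four prescribed doses, so a break in time does not identify one.

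**4. The confirmatory test.** The Davies test asks whether a slope changes at some unknown point along a covariate. In the printed equation the change point is given by the intervention term. The test fits a segmented model in dose, which is not the model printed.

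**5. Illustration on assumed data.** One simulated data set was drawn for each true threshold: 50 women × 12 weeks, participant SD 10, residual SD 6, slope −0.3 per minute above the threshold, and achieved dose varying around the prescribed totals. These inputs are assumptions, not figures from the article. The printed equation was fitted with intervention coded by arm. The comparison is a random-intercept model with a hinge on dose (no time term), searched in steps of 5 minutes.

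| True threshold (min/week) | Printed equation: time, intervention, time after | Dose-hinge model: threshold |
|---|---|---|
| 60 | −0.23, −8.02, −0.49 | 70 |
| 90 | −0.03, −4.09, −0.36 | 85 |
| 120 | −0.43, −4.90, 0.17 | 120 |

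Nothing in the middle column is in dose units. With single data sets, the right-hand column shows only that a hinge on dose returns the right kind of quantity; it is no measure of precision.

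**6. Participant index.** If the 600 rows were treated as independent, information on differences between participants would be overstated. With 12 rows each, effective size = 600 / (1 + 11 × ICC): 600/4.3 ≈ 140 at ICC 0.3, 600/6.5 ≈ 92 at 0.5, and 600/8.7 ≈ 69 at 0.7. The ICC values are assumed. This applies only if the formula is fitted literally, against the mixed-effect wording.

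**The case against.** The strongest defence is that the formula is shorthand. The prose says segmented, mixed-effect and dose threshold, and the Davies test points to an estimated breakpoint, so the authors probably intend the right model and printed the wrong equation. A condensed article may also leave random-effects notation to an analysis plan. Much of this stands. The missing participant index is an inconsistency between text and formula, not evidence that no participant effect will be fitted. But intent does not repair the main defect: the article says positively that this equation determines the threshold, so it is a wrong statement and not an omission left to another document.

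A reader might infer more, namely that the intervention term is always 1 in the active arms, that the design therefore has rank 2 of 4 there, that the three active arms are pooled, and that the randomised dose contrast is thrown away. The documents do not support this.
- The rank and pooling results require intervention to be coded 0/1 by arm and weekly data to begin with the intervention. The article states neither, and the contents of its assessment schedule (Table 1) are not available.
- Under the week-six coding, a walking arm has one line for weeks 1 to 6 and another for weeks 7 to 12. That is two intercepts and two slopes, so rank 4.
- The four-group comparison remains in the sample-size basis, and EHP-30 pain is analysed by intention to treat.

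A fair caution also applies to any remedy. The Safety and monitoring section encourages women to exercise within the limits of their symptoms, so symptoms can drive achieved dose as well as the reverse.

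**Conclusion.** Wrong as written. The equation assigned to the dose-threshold analysis has no breakpoint on dose under any of the readings tried, and it does not match the Davies test or the mixed-effect description beside it. Fitted as printed, it yields no threshold in dose units, so the stated threshold question is not answered. This conclusion rests only on the printed equation and the sentences around it; it needs neither the simulation nor the ICC values.

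The claims about rank and pooling of the active arms are conditional on an unstated coding and are not part of the conclusion. The pain endpoint and its group comparison are not affected.

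**What to change.** Replace the equation with a participant-indexed segmented mixed model in the protocol's own weekly dose variable, for example

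Y_it = b0 + u_i + b1·week_t + b2·dose_it + b3·max(dose_it − ψ, 0) + e_it,

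where Y is the weekly Endometriosis Impact Scale score (the only outcome described as weekly), u_i is a participant effect, dose combines duration and heart-rate intensity as already defined, and ψ is the threshold.

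- Estimate ψ with a confidence interval that respects clustering within participants.
- State that the breakpoint test is applied to dose, not to time.
- Describe the achieved-dose threshold as observational, because symptoms may influence how much exercise is done, and support it with the randomised group contrast.
- Say that this model covers weekly symptoms. Quality of life and biomarkers are assessed before and after the intervention, so a weekly model does not provide thresholds for them.

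The cost is protocol or analysis-plan wording and analysis code. The weekly symptom and activity data are already planned, and no extra participants or measurements are needed. The change should be made before outcome data are examined.

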## Primary outcome measures

### Activity data

All participants will be provided with a Garmin Vivosmart5 activity monitor for remote activity tracking and adherence logging. Data regarding heart rate, exercise duration and modality will be collected weekly as part of the study. All participants, including passive controls, will be asked to document any incidental exercise completed outside of the study requirements using the Garmin Vivosmart5 activity monitor. The intensity of the walking and yoga sessions will be determined via obtaining the relative percentage of the average HR against age predicted MHR. Furthermore, internal training loads (TRIMP) will be calculated through: Training load = D x (Δ HR ratio) x 0.86e^1.67(Δ HR ratio)^. Moreover, MET-Minutes will be calculated as a secondary unit to measure exercise load.

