### Survey data

Demographic information, current exercise behaviours (APSS), scores of depression, anxiety and stress (DASS-21), health-related quality of life (EHP-30), sleep (PSQI), self-efficacy (SEE) and open-ended questions regarding treatment, geographical location, fertility and access to care, will be collected pre- and post-intervention. Moreover, symptoms will be tracked weekly via the Endometriosis Impact Scale (EIS) through REDCap, a survey administration software program.

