All other data will be reported as mean ± standard deviation (SD) or median interquartile ranges. Normal distribution will be determined by Shapiro-Wilk’s test and non-normally distributed data will be logarithmically transformed prior to analysis. Pain, as a subset of the EHP-30 is the primary endpoint and will be analysed with an intention-to-treat analysis. A sensitivity (per-protocol analysis) will also be conducted to confirm outcomes. Secondary and exploratory endpoints will be arranged hierarchically as follows; quality of life (EHP-30), depression, stress, anxiety (DASS-21), functional capacity, sleep (PSQI), estradiol, CRP, cortisol. Multiple comparisons will be adjusted for using the Benjamini-Hochberg false discovery rate procedure. Missing data will be managed depending upon the volume of data, complete case analysis will be performed (<5%) for 5–40%, multiple imputation for chained equations or random forest imputation will be employed. Complier average causal effect (CACE) analysis will be employed if compliance varies significantly. Significance will be set at p < 0.05. All statistical procedures will be performed using Statistical Package for the Social Sciences (SPSS; Windows version 31.0, Chicago, IL, USA) and R Studio (2026.07.1).

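### The protocol designates the primary outcome in three conflicting ways, and the weekly regression it calls primary has no named outcome and no sizing of its own

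*Protocol article*

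**What the plan says.** The protocol article assigns primary status in three places.

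- **Section "Primary outcome measures".** It has two parts, Activity data and Survey data. The first covers heart rate, exercise duration and modality from the monitor. The second lists "scores of depression, anxiety and stress (DASS-21), health-related quality of life (EHP-30), sleep (PSQI), self-efficacy (SEE") before and after the intervention, and the EIS every week. Only the biomarkers sit under the secondary heading that follows.
- **Data analysis, first paragraph.** A piecewise mixed-effects regression "will be used to determine the critical threshold for exercise dose (primary outcome"). Dose is aggregated weekly, and the outcome in the equation appears only as Y.
- **Data analysis, second paragraph.** "Pain, as a subset of the EHP-30 is the primary endpoint and will be analysed with an intention-to-treat analysis". It continues: "Secondary and exploratory endpoints will be arranged hierarchically as follows; quality of life (EHP-30), depression, stress, anxiety (DASS-21), functional capacity, sleep (PSQI"), followed by the three biomarkers.

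The sample size paragraph starts from a cited study in which "the mean difference for pain between the control and intervention was 24.74" and then, "for an effect size of d = 1.33 and comparisons between four groups", states that "a sample size of 32 was estimated (alpha at 0.05 and power 0.80"). The target is raised to 50 for attrition and funding. The regression is supported separately by an observation count of 600, which the text presents as a floor.

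**The concern.** The primary outcome fixes what counts as a positive trial, so it has to be one identifiable quantity. Here two paragraphs of the same section name different single primaries, and an earlier section gives primary status to a longer list that the later ranking contradicts. If pain and the dose threshold pointed in different directions, the document would not say which one answers the trial's question, and the choice could be made after the results are known.

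The two candidates also have different foundations. One is sized by a power calculation on a difference between groups. The other is supported by a count of weekly records, without a named outcome, an effect to detect or a stated power.

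**Working it through.** **1. The designations side by side**

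| Item | Outcome sections | Data analysis |
|---|---|---|
| Dose threshold | not listed | primary outcome |
| EHP-30 pain | primary (within EHP-30) | primary endpoint |
| EHP-30 quality of life | primary | secondary/exploratory |
| DASS-21 | primary | secondary/exploratory |
| PSQI | primary | secondary/exploratory |
| SEE | primary | not ranked |
| EIS (weekly) | primary | not ranked |
| Activity data | primary | used to define the dose |
| Biomarkers | secondary | secondary/exploratory |

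Only EHP-30 pain and the biomarkers carry the same status throughout, and even pain shares the primary label with the threshold.

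**2. What the sample size supports**

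Inputs from Data analysis: difference 24.74, d = 1.33, four groups, alpha 0.05, power 0.80. The implied SD is 24.74 / 1.33 = 18.6. Equal allocation is assumed because no ratio is stated.

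One-way ANOVA with k = 4 and Cohen's f = d/2 = 1.33/2 = 0.665. The noncentrality is f² × N = 0.442 × 32 = 14.15, on 3 and 28 degrees of freedom. The smallest balanced design that reaches 0.80 is 8 per arm, N = 32, with power 0.85. The stated figure is therefore reproduced. A one-sided two-sample t-test at 0.05 also gives 8 per arm, 32 over four arms.

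Either route is a comparison of pain between groups. Neither involves a breakpoint, a slope change or a weekly outcome.

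Two qualifications on 32:

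- Setting f = d/2 assumes the most favourable pattern, with two arms at each extreme. With the same range of means, one arm differing from the other three needs 40, equal spacing needs 52, and two arms midway between the extremes needs 56.
- For a single pairwise contrast (two-sided t, alpha 0.05, d = 1.33), power is 0.70 at 8 per arm, 0.80 at 10 and 0.88 at 12. A target of 50 gives about 12 per arm under equal allocation.

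**3. What the regression can draw on**

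Records = participants × measurement occasions.

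- Stated count: 50 × 12 = 600. This reproduces the figure and shows that it presupposes a weekly outcome.
- EHP-30 pain, before and after: 50 × 2 = 100 at most, with no weekly values to pair with weekly dose.
- EIS, weekly: 50 × 12 = 600 only if all 50 participants supply all 12 weeks. At 90% completeness it is 540, and at 80% it is 480. With 32 completers and nothing from dropouts it is 32 × 12 = 384.

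The count of 600 is therefore a maximum for the 12 weeks. The Limitations section itself accepts that attrition may reduce the number of observations. The allowance from 32 to 50 corresponds to a loss of up to 1 − 32/50 = 36%.

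**The case against.** The best defence is that the two primaries play different roles: the threshold is the primary objective and EHP-30 pain is the primary clinical endpoint. The abstract and specifications table support part of this. They separate chronic symptom severity, assessed before and after, from acute symptom impact, assessed weekly, and the EIS is the weekly instrument. The second paragraph of Data analysis opens by turning to the remaining data, which could explain why the EIS is missing from its ranking. This makes EIS the natural candidate for Y. The document never says so, however, and never says which of the two results decides the trial. The conflict between the section heading and the later ranking also remains.

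Four stronger readings are tempting, and the documents do not support them.

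- **Every listed scale tested as a primary at an unadjusted 0.05.** Data analysis specifies a ranking and a Benjamini-Hochberg adjustment, which for independent true null hypotheses holds the chance of any false positive at 5%. What is open is which tests form the family.
- **A difference in activity reported as trial success.** The monitor data are described as tracking and adherence logging, and they define dose in the regression. No test of activity as efficacy is planned, so the primary heading is simply misplaced over them.
- **EHP-30 pain entered in the weekly regression.** The protocol does not say this; it leaves Y unnamed.
- **A mismatch with the registry.** The registry entry is not shown, so none can be alleged.

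Nor is this detail that an article leaves to a fuller plan. The statements conflict, and a later plan could reconcile them only by overriding at least one.

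**Conclusion.** The point holds. Two different single primaries are named in one section, and at least three instruments or subscales (DASS-21, PSQI, EHP-30 quality of life) are primary in one place and secondary or exploratory in another. SEE and EIS are primary under the heading and unranked afterwards. The sample size supports a between-group comparison of pain. The threshold analysis rests on a count of 600 that EHP-30 cannot supply (at most 100 records) and that EIS reaches only with complete data.

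This rests on one inference: the sample size paragraph says only pain, and reading it as EHP-30 pain relies on the endpoint named in the next paragraph. If the cited study used another scale, the link between the sizing and EHP-30 pain would be weaker, but the conflict of designations would be unchanged.

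The consequence is ambiguity about which result decides the trial. No inflated error rate can be computed from the text. It should be corrected before any data are analysed.

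**What to change.** 1. Designate one primary endpoint that decides the trial. EHP-30 pain by intention to treat is the one the existing sample size supports. The threshold is the trial's stated purpose, so the sponsor may prefer to keep it as primary. It then needs its own sizing on a named outcome, and pain moves down.
2. Name EIS as Y in the threshold regression and give that analysis an explicit place in the hierarchy.
3. Describe 600 as the maximum number of weekly records, and state the number expected after attrition and missed weeks.
4. Move DASS-21, PSQI, SEE and EHP-30 quality of life out of the Primary outcome measures section, and give SEE a place in the ranking. Relabel activity data as exposure and adherence.
5. State which tests form the Benjamini-Hochberg family.

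The cost is wording before analysis, with no change to data collection. The exception is a threshold kept as primary, which needs a new sample size justification.

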## Exercise intervention

This study will involve a remote 12- week exercise intervention for regional, rural and remote Australian women living with endometriosis. Participants will be randomly allocated into one of four groups: passive control, active control, shorter duration, longer duration. Allocation will be determined by simple randomization using a randomization table created by computer software (REDCap), with the sequence accessible to one member of the research team only (KB). Central randomization will be utilized for allocation. The passive control will involve usual care, and the active control group will complete 10 min of yoga, three times per week for the 12 weeks (supplementary file 1). The shorter and longer duration exercise groups will complete 10 min of yoga, three times per week in addition to a walking intervention. The shorter duration group will commence at 60 min per week (3 × 20-minute sessions), and the longer duration group will commence at 120 min per week (3 × 40-minute sessions). After six weeks, the total duration in each walking group will be increased to 90 min and 150 min, respectively, with each group increasing session duration by 10 min. Participants will be encouraged to walk as fast as comfortably possible for 1 min, every 5 min of each session.

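### The missing-data method for the primary endpoint depends on how much is missing, leaves a choice open at 5–40%, and stops at 40%; one pre-specified multiple-imputation rule should replace it

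*Protocol article*

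**What the plan says.** In the protocol article, under Data analysis, EHP-30 pain "is the primary endpoint and will be analysed with an intention-to-treat analysis". The same paragraph makes the handling of missing data depend on its volume: "complete case analysis will be performed (<5%) for 5–40%, multiple imputation for chained equations or random forest imputation will be employed". It gives no method above 40%. It does not say what the percentage is counted on, or which variables enter an imputation model.

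Under Survey data, the EHP-30 is collected before and after the intervention only, whereas "symptoms will be tracked weekly via the Endometriosis Impact Scale (EIS", through REDCap.

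On size, Data analysis reports that "a sample size of 32 was estimated (alpha at 0.05 and power 0.80" and then: "Factoring in attrition and funding availability, the target sample size was set to 50". No attrition rate is stated. The Limitations section warns that adherence may be low and that attrition may follow.

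**The concern.** A woman who leaves before the post-intervention survey has no primary endpoint unless the missing-data rule supplies one, so this rule is part of the primary analysis. As written it has three weaknesses.

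- **Chosen after the fact.** The method is known only once the amount of missing data has been seen. In the middle band two procedures are joined by an *or* with nothing to decide between them.
- **Inconsistent label.** In the lowest band the rule omits randomised women from an analysis called intention-to-treat.
- **Incomplete.** In the highest band there is no rule.

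At stake is the credibility of the primary result in a trial with about 12 women per arm. It is delivered remotely, is self-directed and foresees symptom exacerbation, so symptom-related dropout is plausible. If that dropout is concentrated in the exercise arms, an analysis of completers flatters exercise.

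**Working it through.** **Inputs from the protocol article (Data analysis, Exercise intervention).** Mean difference 24.74 and d = 1.33, so the implied SD is 24.74/1.33 = 18.6. Estimated N = 32, target N = 50, alpha 0.05, power 0.80. Four arms by simple randomisation, so about 50/4 = 12.5 per arm.

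**1. The plan's own figure.** 32 can be reproduced in two ways:
- one-sided two-sample t-test: 7.77, rounded up to 8 per arm, × 4 = 32;
- four-group F-test with f = 1.33/2 = 0.665: N = 28.9, rounded up to 8 per arm = 32.

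A two-sided t-test would give 10 per arm, 40 in all. The article does not say which method was used. What follows takes 32 as stated.

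**2. Loss the sizing tolerates.** (50 − 32)/50 = 18/50 = 36%.

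**3. The bands as counts of 50 women.** This assumes that the percentage refers to the primary endpoint over all randomised women.

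| Band | Women missing | Method stated |
|---|---|---|
| below 5% | 0–2 (2/50 = 4%) | complete case |
| 5–40% | 3–20 (20/50 = 40%) | one of two imputation methods |
| above 40% | 21 or more (21/50 = 42%) | none |

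A loss of 18 falls in the middle band; 21 − 18 = 3 further losses reach the gap.

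**4. Chance of reaching the gap.** P(X ≥ 21) for X ~ Binomial(50, p). The article gives no p, so a range is shown.

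| Assumed attrition p | P(more than 40% missing) |
|---|---|
| 20% | 0.03% |
| 25% | 0.6% |
| 30% | 4.8% |
| 36% | 22.9% |
| 40% | 43.9% |

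**5. Lowest band, worst case.** The two largest of 12 standard normal values average about 1.63 and 1.12, a sum of 2.75. If exactly those two women are missing, the mean of the other 10 shifts by 2.75/10 = 0.27 SD, and 0.27 × 18.6 is about 5 points. This is a bound, not an expectation.

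**6. Bias if symptoms drive dropout.** This is a large-sample calculation with no true effect. Assumptions, none of them from the article: baseline–post pain correlation 0.5, EIS–post pain correlation 0.7, baseline–EIS correlation 0.5 × 0.7 = 0.35, SD 18.6. In the exercise arm the log-odds of leaving rise by 0.5 (weak) to 2 (strong) per SD of EIS. Controls leave at random at the same overall rate. The estimate is the baseline-adjusted (ANCOVA) arm difference among completers.

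- 10% dropout, weak selection: about −0.5 points.
- 36% dropout, strong selection: about −4.4 points, which is 4.4/24.74 = 18% of the difference used for sizing.
- Both arms leaving by the same mechanism: about 0 (within 0.11 points).

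Steeper selection than assumed would give more. Imputation that includes the EIS removes the bias here, but only because dropout was assumed to depend on the EIS.

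**The case against.** The strongest reply is that this is a condensed article, that imputation detail belongs in a full protocol or analysis plan, and that the gaps are small. Several parts of that stand, and they rule out stronger readings that a reader might draw.

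- **That the plan ignores the weekly EIS.** The article is silent on imputation predictors and neither includes nor excludes the EIS. Using it is a recommendation here, not the correction of an error.
- **That a single random-forest fill-in is planned.** The text does not say so. A random forest is a standard conditional model inside chained equations. Only the unresolved choice between two named options is established.
- **That the trial plans for 36% attrition and so for a case without a rule.** 36% is a derived ceiling. The target of 50 also reflects funding, and 36% lies inside the imputation band. At 25% attrition the gap is very unlikely.
- **That the 40% limit applies within each arm.** Arms of about 12 would cross it far more often, but nothing in the text applies the limit by arm.
- **That dropping women below 5% is serious.** It touches at most 2 women. Complete case at that level is a common convention, and intention-to-treat is often used to mean analysed as randomised.

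The bias range also rests on a one-sided dropout mechanism. The Safety and monitoring section offers women with exacerbations a meeting and modifications, which may weaken it. Multiple imputation with over 40% missing in arms of about 12 is itself fragile.

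What the reply does not remove is the printed rule: it is selected by the observed missingness, leaves a choice open in the middle band, and ends at 40%.

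**Conclusion.** The point holds for the rule as printed. In the lowest band up to 2 of 50 randomised women are dropped under an intention-to-treat label. At 3–20 missing, two methods are allowed without a criterion. From 21 missing there is no method, three women beyond the largest loss that the stated sizing tolerates. The chance of reaching that gap is 0.6% to 23% for assumed attrition of 25% to 36%.

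The possible cost of analysing completers is about −0.5 to −4.4 points in favour of exercise at 10–36% dropout. This requires that exercising women leave because of symptoms and controls do not, and it rests on the assumed correlations and selection strengths. It is about zero if all arms lose women by the same mechanism. The matter is worth fixing before data are seen, but it does not threaten the design.

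**What to change.** Replace the three bands with one pre-specified primary rule: analyse EHP-30 pain in all randomised women by multiple imputation with chained equations, whatever the amount missing. The imputation model should contain arm, baseline EHP-30 pain and a summary of the weekly EIS observed up to dropout. A random forest may be used only as the conditional model within multiple imputation.

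Keep complete case as a sensitivity analysis. Add a delta-shift sensitivity analysis that makes the imputed outcomes of dropouts progressively worse.

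The cost is a few sentences and a little more analysis work. No new data are needed, because the EIS is already collected weekly. Intervals will be wide if much is missing in arms of about 12, so results with more than 40% missing should be reported with that caution.
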